### Randomization and Intervention

Enrolled participants were randomized to 1 of 4 treatment groups using permuted block randomization. Random blocks of 4 were generated using the R package “blockrand” [32] for male and female participants separately. Allocation was concealed using sealed, opaque, numbered envelopes. The study coordinators and participants were not blinded to group allocation.

Participants randomized to intervention groups were provided with supplements to be taken with their meals (Table 2). Participants in the BCAA group (group B) were instructed to consume 1 capsule of BCAA supplements thrice daily with their main meal. Participants in the BCAA and tryptophan group (group C) were instructed to consume 1 capsule of BCAA thrice daily and 1 tablet of tryptophan supplement twice daily. Participants in the BCAA and methionine group (group D) were instructed to consume 1 capsule of BCAA and 1 capsule of methionine supplement thrice daily.

**Table 2. T2:** Description of diets and interventions for study groups.

Diet name or group	Diet or intervention description
Group A: control	Regular diet containing 18% to 19% of total energy from protein
Group B: BCAA^a^	Regular diet+3 doses of BCAAs (L-leucine 300 mg, L-isoleucine 150 mg, and L-valine 150 mg)
Group C: BCAA+tryptophan	Regular diet+3 doses of BCAAs (L-leucine 300 mg, L-isoleucine 150 mg, and L-valine 150 mg)+2 doses of L-tryptophan (1000 mg)
Group D: BCAA+methionine	Regular diet+3 doses of BCAAs (L-leucine 300 mg, L-isoleucine 150 mg, and L-valine 150 mg)+3 doses of L-methionine (500 mg)

a BCAA: branched-chain amino acid.

### Primary Outcome Measurements

Appetite and total food intake were the primary outcomes in this study. They were measured using plasma FGF-21, ghrelin, self-reported appetite, and dietary intake.

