**Methods:**

This randomized controlled clinical trial recruited 110 adults (aged 65-80 y; BMI 20-35 kg/m^2^). Participants were randomly allocated to four 4-week intervention groups: (1) control (no supplementation), (2) BCAAs, (3) BCAAs+tryptophan, or (4) BCAAs+methionine. All participants received a controlled diet, with intervention groups additionally receiving amino acid supplements. The primary outcomes are appetite assessed via self-reports and fibroblast growth factor 21 levels (a marker of protein appetite), and energy intake quantified from dietary intake data. Secondary outcomes include body composition, cardiometabolic health, gut microbiota, blood biomarkers, sleep, and physical performance. Descriptive statistics will be used to summarize participant characteristics. Linear mixed models will assess intervention effects, with and without adjustment for relevant covariates. Diet-specific self-reported appetite and palatability scores will be analyzed using generalized additive mixed models.

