### Statistical Analysis

All statistical analyses will be conducted using R software, with significance set at *P*<.05. The analysis will follow the following two approaches: (1) within-subject comparisons using paired sample *t* tests (via the “t.test” function in stats package) to assess overall changes from baseline (habitual diet) to after intervention and (2) between-group analyses of RCT findings across all 4 groups, maintaining treatment assignment integrity and excluding dropouts.

A 1-way ANOVA will be used to examine across the 4 diet groups in follow-up measurements. A linear model (model 1) will be fitted with follow-up values as the outcome and baseline measurements as covariates to assess the effect of the intervention. A second model (model 2) will further adjust for potential confounders, including age, sex, BMI, and physical activity level.

Self-reported appetite and palatability data specific to each diet will be analyzed using the R package *mgcv* with the gam function [44]. Generalized additive mixed models will be applied to assess the effects of dietary interventions on appetite scores. For BCAA levels and metabolites, relative changes (fold changes) will be calculated as the ratio of final to baseline values. A 1-sample *t* test (null hypothesis of fold change=1) will be used to test whether the change from baseline is significant compared to final. To compare differences in fold change across groups, models will be fitted using follow-up measurements as outcomes, adjusting first for baseline values. A second model will further adjust for covariates such as age, BMI, sex, and physical activity levels. Dropouts will be treated by exclusion for analysis.

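### The article gives two different lists of primary outcomes and one P<.05 rule for everything, and names no outcome or model that decides the trial

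*Protocol article*

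**What the plan says.** **Primary outcomes, Abstract (Methods).** "The primary outcomes are appetite assessed via self-reports and fibroblast growth factor 21 levels", together with "energy intake quantified from dietary intake data". That makes three measures, and ghrelin is not among them.

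**Primary outcomes, Primary Outcome Measurements.** "Appetite and total food intake were the primary outcomes in this study", followed by "They were measured using plasma FGF-21, ghrelin, self-reported appetite, and dietary intake". That makes four measures, with ghrelin included and intake worded differently.

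**Error rule, Statistical Analysis.** "All statistical analyses will be conducted using R software, with significance set at *P*<.05". Under this one threshold the section places paired t tests within participants, an ANOVA ("A 1-way ANOVA will be used to examine across the 4 diet groups in follow-up measurements"), a baseline-adjusted linear model (model 1), a model with further covariates (model 2), and additive mixed models for the appetite scores. None of these is called the primary analysis. The Abstract instead speaks of linear mixed models for the intervention effects.

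**Sample size, Study Design.** The calculation uses FGF-21 only, at a single alpha of .05. No section makes FGF-21 the single primary outcome.

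**Hypotheses, Introduction.** These are set against the control diet. Appetite and energy intake should rise with BCAA and with BCAA plus methionine, and tryptophan should mitigate the rise.

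**The concern.** Two sections of one article disagree on what is primary, and the text does not say how a primary claim would be reached. A significant result on FGF-21, ghrelin, self-reported appetite or intake could each be presented as the main finding, from any of several models. Ghrelin could count as primary or not according to which section a reader relies on.

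This matters more than usual here. The trial is open label, and the Strength and Limitations section itself accepts that self-reported outcomes may carry expectation bias. Data collection is complete, so the list has to be settled before results by group are known if it is to protect against selective emphasis.

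**Working it through.** **The plan's own figure.** The article states no overall error rate, so there is none to reproduce. The only related figure is the FGF-21 sample size of 25 per group. It is used below for the group size and, at the end, for its difference and SD. Whether 25 per group gives the stated power is a separate question and does not affect the error rates.

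**The two lists side by side**

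| Measure | Abstract | Primary Outcome Measurements |
|---|---|---|
| Self-reported appetite | yes | yes |
| FGF-21 | yes | yes |
| Ghrelin | no | yes |
| Intake | energy intake | total food intake, from dietary intake |
| Number of measures | 3 | 4 |

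**Inputs for the error rate**
- From the article: 4 groups, 25 per group, P<.05 (taken as two-sided, as in the sample size), and 3 or 4 primary measures.
- Assumed: no true effect on any outcome; a claim is made if any primary outcome is significant; normal data with equal variance; correlation between outcomes of 0 or 0.5, because the article gives none.
- Simplification: every outcome, including the appetite scores, gets one test of the stated kind, although the article assigns those scores to additive mixed models.

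**A. One four-group ANOVA per outcome (the named test)**
- Three independent outcomes: 1 − 0.95³ = 1 − 0.857 = 14.3%.
- Four independent outcomes: 1 − 0.95⁴ = 1 − 0.815 = 18.5%.
- By simulation at correlation 0.5: about 13% and 16%.

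**B. Each of three supplemented arms against control, unadjusted (not stated in the analysis section)**
- One outcome: about 12.5% by simulation. This is below 1 − 0.95³ = 14.3% because the three comparisons share the control group.
- Three outcomes: 1 − (1 − 0.125)³ = 33% if independent; about 29% at correlation 0.5.
- Four outcomes: 1 − (1 − 0.125)⁴ = 41% if independent; about 35% at correlation 0.5.

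**C. The same comparisons, made only after a significant ANOVA**
- By simulation, about 10–12% for three outcomes and 13–15% for four, over correlations 0.5 to 0.

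Choosing between the ANOVA, model 1 and model 2, or drawing on the paired tests, would add further chances. These are not counted.

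**Cost of adjustment.** Holm's first step with four outcomes is at .05/4 = .0125. The plan's own inputs give a difference of 0.30 × 149.4 = 44.82 pg/mL, and 44.82/70 = 0.64 SD. For one supplemented arm against control at 25 per group (two-sided, variance pooled over the four groups), power is 0.61 at .05 and 0.39 at .0125. If two arms were pooled against the other two (50 v 50), it would be 0.89 and 0.74. The article specifies neither contrast, so these figures are illustrations only.

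**The case against.** **The mismatch is small.** Both sections name the same two constructs, appetite and intake. The Introduction hypothesises on energy intake, and food records are converted to nutrients, so total food intake is probably loose wording. That is fair for intake. It does not settle ghrelin, which is primary in one section only.

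**Multiplicity rules belong in the analysis plan.** A procedure may exist in a document not shown here, so its absence from the article is no finding, and the same holds for control across metabolite and microbiome families. What stands is what the article states: two conflicting primary lists and one threshold for all analyses. An analysis plan would not remove the contradiction in the published text.

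**The error rate depends on the decision rule.** If every primary outcome had to be significant, the error would not exceed 5%. The article states neither that rule nor the opposite one, which is the point at issue.

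**A stronger reading is tempting.** A reader might infer that the trial carries a 35–40% chance of a false primary claim. The documents do not support this as a headline. It needs four outcomes, three unadjusted comparisons with control on each, and an assumed correlation. The analysis section lists no pairwise comparisons, and the predicted increases concern only two of the three supplemented arms. A reader might also infer that ghrelin was added or dropped after the fact. Nothing shows this: the trial was registered in April 2021, before recruitment began, and the registered outcomes are not available here.

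**Conclusion.** The point holds as an internal contradiction combined with an undefined route to the primary claim. The primary set has three members in the Abstract and four in the Methods, one P<.05 threshold covers all analyses, and no outcome or model is named as deciding.

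If any significant primary outcome may be claimed, the chance of at least one false positive on the named ANOVA is about 14% (three outcomes) to 19% (four) under independence, and about 13–16% at an assumed correlation of 0.5. The higher figures, about 29–33% and 35–41%, apply only if each supplemented arm is compared with control without adjustment. The hypotheses suggest such comparisons, but the analysis section does not state them. Every version calculated under the any-outcome rule exceeds the nominal 5%. The exact size cannot be fixed from the article.

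**What to change.** Before outcome data are compared by group:

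1. Reconcile the Abstract and the Primary Outcome Measurements section to one list consistent with the registered primary outcomes. State ghrelin explicitly as in or out, and define intake as energy intake in kJ/day.
2. Either name one primary outcome and one deciding model, with the rest secondary, or apply Holm across the listed primary outcomes with one stated test per outcome. The baseline-adjusted model 1 would suit FGF-21 or energy intake. The article describes appetite ratings only during the intervention, so that outcome would need its additive mixed model named instead.
3. If analysis has already begun, report the date on which the list was fixed. The article is unclear on this: the Abstract says cleaning and analysis are in progress, while the Results section schedules them from March 2026.

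**Cost.** The reconciliation is a matter of wording. Holm over four outcomes starts at .0125 and lowers power per outcome, as illustrated above. A single primary outcome avoids that loss, but the other measures then become supportive only.

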#### Dietary Intakes

Participants’ dietary intake were recorded in 2 phases: a 7-day habitual intake period prior to the intervention and a 4-week intervention phase during which study-provided foods were consumed. To assess habitual dietary intakes, participants completed a 7-day weighed food record (7dWFR) prior to the dietary intervention. A kitchen scale (IKEA ORDNING) was supplied to each participant to complete the 7dWFR. Dietary information was recorded by participants manually in a 7-day food diary or via a mobile app (Research Food Diary) [33]. The 7dWFR was adapted from Henderson et al [34].

During the intervention phase, participants used a study dietary record booklet, which included a list of all study meals, to document their intake. Participants allocated to intervention groups also recorded supplement consumption throughout the intervention period in the same booklet. Individual dietary intakes (both habitual and intervention) were inputted into FoodWorks 10 Professional with the Australian Food, Supplement and Nutrient Database 2013 [31,35] and converted into nutrients intakes.

#### Blood Sample and FGF-21

Approximately 50 mL of fasting blood (20 mL serum and 30 mL plasma) was collected by a qualified blood collector at baseline and final assessment. Serum was collected into 8.5 mL serum separator tube II Advance tube (BD Vacutainer ref 367,958; Becton Dickinson). Cardiometabolic health was measured using serum markers, including electrolytes, urea, and creatinine; calcium and phosphate; protein and albumin; AAs; triglycerides, total cholesterol, and high-density lipoprotein cholesterol; glucose and insulin; C-reactive protein; IGF-1; leptin; and liver function markers, including alanine aminotransferase, aspartate aminotransferase, and lactate dehydrogenase.

Plasma was collected into 10 mL ethylenediaminetetraacetic acid tubes (BD Vacutainer; Becton Dickinson) for measurement of circulating proteins, including FGF-21, ghrelin, cytokines, and other relevant biomarkers. Targeted protein concentrations were quantified using enzyme-linked immunosorbent assay. EDTA blood sample will also be used for cytokine analysis. Additional blood samples will be collected for isolation of peripheral blood mononuclear cells for immune profiling.

#### Palatability and Appetite Questionnaires

Visual analog scale (10-cm horizontal line) questionnaires were used to determine participants’ palatability of study foods and appetite during the intervention [36]. Participants completed palatability and appetite questionnaires on every fourth day of each intervention week (days 4, 11, 18, and 25).

### Secondary Outcome Measurements

#### Self-Reported Questionnaire

Participants completed a set of questionnaires before and after the dietary intervention. These include a physical activity questionnaire, from which the Physical Activity Scale for the Elderly score was calculated, and the Sleep Apnea Global Interdisciplinary Consortium questionnaire, which assessed sleep quality [37,38]. Participants also self-reported their demographic details, medical history, tobacco and alcohol use, and daily habits through questionnaires before starting the study.

#### Physical Activity and Sleep Patterns

Participants were provided with Fitbit devices (version Fitbit Inspire 2; Google) to enable biometric data collection (daily step count, heart rate, and sleep duration and quality) through Fitabase’s proprietary API tool [39,40]. Participants reviewed Fitbit’s privacy policy during screening interview and agreed to Fitbit’s terms and conditions before making a study account. Device charging and data syncing were tracked through the Fitabase platform. Participants were instructed to wear the Fitbit watch 24 hours a day during both the baseline week (7-day preintervention phase) and the 4-week intervention period.

#### Blood Pressure

Systolic and diastolic blood pressure were measured twice, to the nearest 2 mm Hg, 1 min apart after 5 minutes of quiet rest in a seated position [41], using automated sphygmomanometers on the right arm of participants during baseline and final assessments.

#### Body Composition

Participants fasted overnight prior to body composition assessment. Body weight, fat mass, and fat-free mass were measured using air displacement plethysmography (BodPod; COSMED). To minimize potential error from isothermal air trapped in clothing and hair, participants wore tight-fitting clothes and a Lycra swim cap. Body fat percentage was determined by the Siri equation [42]. The procedure took no longer than 10 minutes.

#### Physical Capacity Assessment

Handgrip strength, repeated chair stand, and habitual walking speed were tested to assess participants’ physical performance at baseline and final assessments. Hand grip strength was assessed with participants seated on a straight-backed chair. The shoulders were positioned in a neutral abduction with the arms in a neutral rotational position. The wrists were positioned at 0° to 30° extension and 0° to 15° flexion. Participants were instructed to squeeze the dynamometer with maximum effort for a duration of 10 to 30 seconds. Assessments were conducted with both hands (2 measurements each) using the Jamar dynamometer (Promedics), with 30-second rest intervals. A chair without armrests and a seat height of 40 cm was used for the repeated chair stand assessment. The test involved measuring the time taken for participants to successfully complete 5 repeated chair stands without using their arms. Participants’ mobility was evaluated using a 6-meter walking test, during which each participant was asked to walk at normal speed over a 6-meter course [43].

#### Gut Microbiome and Short-Chain Fatty Acid

Stool samples were collected within 48 hours prior to baseline and final assessments. Participants were provided with stool sample collection kits, including a fecal container (Sarstedt feces tube, with blade, screw cap; 54×28 mm and white), a thermal bag (Thermabag), and a small ice pack during the screening interview and baseline assessment. Written instructions on sample collection, storage, and transportation were provided to participants during the screening interview. Participants recorded the time and date of the collection and stored the samples in the freezer immediately after collection. Participants were also asked to minimize the time samples remain out of the freezer to <2 hours when delivering them to the clinic on assessment day. Samples were stored at –80 °C immediately upon receipt.

Microbial DNA will be extracted using the SPINeasy DNA Pro Kit for Feces (MP Biomedicals), and bacterial community composition was analyzed via 16S ribosomal RNA gene sequencing targeting the V3-V4 region, following established methods previously described by Ribeiro et al [11]. Raw sequencing data will be processed using validated bioinformatics pipelines (DADA2) to generate amplicon sequence variants. Downstream analyses will be performed using R software (version 4.6.0; R Foundation for Statistical Computing) to assess microbial diversity and relative taxonomic abundance. Differences in overall gut microbiome composition and differences in specific taxa between intervention groups and across time points will be assessed using appropriate univariate, multivariate, and mixed-effects statistical approaches.

Fecal short-chain fatty acid (acetate, butyrate, and propionate) will be quantified using nuclear magnetic resonance, as previously described [11]. Short-chain fatty acid concentrations will be expressed relative to sample weight and analyzed to assess changes over time and between intervention groups.

#### Urinary Urea

Participants were provided with a 4-L urine container to collect a 12-hour urine sample prior to baseline and final assessments. Samples are stored at 4 °C environments following each collection. Total weight and volume are measured by the study investigator prior to sample aliquoting. Aliquoted samples are stored in an −80 °C fridge for further analysis. These samples will be used to assess participants’ protein intake. Urea concentrations will be quantified using standard enzymatic assays in an accredited laboratory, and total urinary urea excretion will be calculated based on urine volume and concentration.

#### Other Measures

Participants received weekly phone calls from a study investigator on every third day of the week during the intervention period. The purposes of the phone calls were to (1) remind participants to complete the palatability and appetite questionnaires on the following days, (2) ask participants how they managed their diet, and (3) ask if additional nonstudy foods were consumed.

### Monitoring

#### Data Management and Biospecimen Storage

A Research Data Management Plan has been created as per Sydney Local Health District guidelines. A 3-digit, deidentified number has been created and assigned to participants. All collected participant data are repersonalized using the assigned 3-digit number for the purposes of data storage. Deidentified data are stored securely on REDCap (Research Electronic Data Capture; Vanderbilt University), and backups are stored in a password-protected computer file within a secured area of the CPC and only accessed by study investigators. Hard copy files are stored in a securely locked area at CPC and accessed only by the study investigators.

Collected biospecimens were numbered sequentially. A sample manifest is maintained to link sample numbers to participant codes. All biospecimens are stored in secured temperature-monitored −80 °C freezers at CPC. The manifest includes the number of samples, date of collection, sample type, and amount. Sample analysis performed in an accredited laboratory may reveal information that may be important for the health of the participant. Health risk factors for metabolic diseases may be identified (glucose, insulin, triglycerides, total cholesterol, and high-density lipoprotein cholesterol), and participants will be informed if abnormal results are identified.

#### Adverse Events

This study has been identified as a relatively low-risk study. Participants were instructed to contact emergency services immediately if they experienced any food allergy or intolerance symptoms during the study and to contact the study coordinator as soon as possible to notify them of the incident. Any unexpected and related serious adverse events arising from this study were reported to the Human Research Ethics Committee in accordance with relevant guidelines.

### Statistical Analysis

All statistical analyses will be conducted using R software, with significance set at *P*<.05. The analysis will follow the following two approaches: (1) within-subject comparisons using paired sample *t* tests (via the “t.test” function in stats package) to assess overall changes from baseline (habitual diet) to after intervention and (2) between-group analyses of RCT findings across all 4 groups, maintaining treatment assignment integrity and excluding dropouts.

A 1-way ANOVA will be used to examine across the 4 diet groups in follow-up measurements. A linear model (model 1) will be fitted with follow-up values as the outcome and baseline measurements as covariates to assess the effect of the intervention. A second model (model 2) will further adjust for potential confounders, including age, sex, BMI, and physical activity level.

Self-reported appetite and palatability data specific to each diet will be analyzed using the R package *mgcv* with the gam function [44]. Generalized additive mixed models will be applied to assess the effects of dietary interventions on appetite scores. For BCAA levels and metabolites, relative changes (fold changes) will be calculated as the ratio of final to baseline values. A 1-sample *t* test (null hypothesis of fold change=1) will be used to test whether the change from baseline is significant compared to final. To compare differences in fold change across groups, models will be fitted using follow-up measurements as outcomes, adjusting first for baseline values. A second model will further adjust for covariates such as age, BMI, sex, and physical activity levels. Dropouts will be treated by exclusion for analysis.

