## Results

Recruitment commenced in April 2022, with the original recruitment period planned for completion within 2 years. However, recruitment was delayed due to COVID-19–related lockdowns and associated restrictions. Enrollment was completed in November 2025.

In total, 208 individuals were screened, of whom 195 were eligible to attend the screening interview. Following screening, 109 participants were enrolled and randomized to treatment groups. Of these, 100 participants completed the 4-week intervention, and 9 were lost to follow-up.

Participants’ baseline characteristics are summarized in Table 3; no statistically significant differences were observed across the 4 intervention groups.

**Table 3. T3:** Participants’ baseline characteristics by randomly assigned diet treatment group.

Characteristic	Overall (n=100)	Control (n=25)	BCAA^a^ (n=24)	BCAA+tryptophan (n=26)	BCAA+methionine (n=25)
Age (years), mean (SD)	71.1 (4.2)	71.2 (4.5)	70.7 (4.1)	71.8 (4.3)	70.6 (4.1)
BMI (kg/m^2^), mean (SD)	27.3 (4.0)	27.8 (3.3)	27.8 (4.6)	27.5 (4.3)	26.2 (3.7)
Physical Activity Scale for the Elderly (points), mean (SD)	146.3 (67.9)	157.2 (66.2)	157.2 (65.8)	116.8 (68.6)	155.5 (65.9)
Weight (kg), mean (SD)	74.4 (12.3)	75.1 (9.8)	76.8 (11.6)	73.1 (13.9)	72.8 (13.7)
Body fat (%), mean (SD)	38.9 (8.9)	40.3 (8.6)	38.3 (11.4)	39.4 (7.1)	37.4 (8.2)
Fat mass (kg), mean (SD)	29.1 (9.0)	30.2 (7.5)	29.8 (11.3)	29.1 (8.7)	27.3 (8.4)
Grip strength (kg), mean (SD)	26.6 (9.0)	26.1 (9.8)	27.5 (10.0)	26.9 (8.2)	26.0 (8.4)
High education^b^, n (%)	90 (90.0)	22 (88.0)	22 (91.7)	23 (88.5)	23 (92.0)
Ex-smoker, n (%)	41 (41.0)	9 (36.0)	8 (33.3)	11 (42.3)	13 (52.0)
Born in Australia, n (%)	66 (66.0)	17 (68.0)	14 (58.3)	19 (73.1)	16 (64.0)

a BCAA: branched-chain amino acid.

b High education includes any education obtained after high school, whereas low education includes completion of high school or below.

All outcome data collection has been completed. Data cleaning and statistical analyses are scheduled to commence in March 2026, with final analyses expected to be completed by December 2026. Results from this trial are anticipated for publication in 2027.

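### For outcomes measured before and after the intervention, three between-arm analyses are stated and none is named as deciding: one ignores baseline, one omits the sex stratum, and the abstract names a different model

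*Protocol article*

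**What the plan says.** The Statistical Analysis section of the protocol article gives three between-arm analyses in sequence:

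- "A 1-way ANOVA will be used to examine across the 4 diet groups in follow-up measurements". It has no baseline term.
- "A linear model (model 1) will be fitted with follow-up values as the outcome and baseline measurements as covariates". It has baseline but no sex term.
- "A second model (model 2) will further adjust for potential confounders, including age, sex, BMI, and physical activity level".

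All share one 5% significance level. None is called primary, and none is restricted to particular outcomes. The abstract's Methods paragraph says instead: "Linear mixed models will assess intervention effects, with and without adjustment for relevant covariates". The only mixed models in the Statistical Analysis section are for questionnaire scores: "Generalized additive mixed models will be applied to assess the effects of dietary interventions on appetite scores".

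Under Randomization and Intervention, the permuted blocks were generated "for male and female participants separately", so sex is a stratification factor. In the Results, the text before Table 3 says that "no statistically significant differences were observed across the 4 intervention groups". Table 3 gives the Physical Activity Scale for the Elderly (PASE) as 116.8 in the BCAA+tryptophan arm and 155.5 to 157.2 in the other three.

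**The concern.** Three analyses of one outcome can give three answers, and the article does not say which one counts. They are not equally good. The ANOVA of follow-up values throws away a baseline that was collected for blood markers and, through the 7-day weighed record, for energy intake. Model 1 leaves out the factor on which randomisation was stratified. Only model 2 contains activity, the one Table 3 variable with a sizeable gap, and that gap lies in the tryptophan arm. The trial is open-label and outcome data collection is complete, so the deciding model should be fixed before results are examined.

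The meaning of activity level in model 2 is also open. PASE is taken before and after the intervention, and Fitbit data come from the baseline week and from the intervention weeks. Some of these measures are post-randomisation.

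**Working it through.** **1. The plan's own figure.** From Study Design: SD 70 pg/mL, control mean 149.4 pg/mL, 30% difference, two-sided alpha 0.05, 80% power, 25 per group. The difference is 0.30 × 149.4 = 44.82 pg/mL, so d = 44.82/70 = 0.640. A pairwise comparison needs 39 per arm (40 by exact t). The 4-group F test needs 37, 55 or 28, depending on whether one arm differs, the means follow the least favourable pattern, or two arms differ from two. An unadjusted ANOVA therefore does not reproduce 25 per group. That is a separate matter; it enters here only because an analysis without baseline starts from low power.

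**2. What baseline adjustment is worth.** Adjusted effect size = d/√(1 − ρ²), where ρ is the baseline–follow-up correlation. The noncentrality is this × √(25/2). Residual df are 96 without baseline and 95 with it. The article gives no ρ, so a range is assumed.

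| Assumed ρ | Effect size | Noncentrality | Pairwise power | Equivalent n per arm, 25/(1 − ρ²) |
|---|---|---|---|---|
| no baseline term | 0.640 | 2.26 | 0.61 | 25 |
| 0.5 | 0.739 | 2.61 | 0.73 | 33 |
| 0.6 | 0.800 | 2.83 | 0.80 | 39 |
| 0.7 | 0.897 | 3.17 | 0.88 | 49 |

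**3. Leaving sex out of model 1.** Stratified allocation balances sex across arms, so the contrast is not biased. The model's standard error still carries the between-sex variance. If sex explains a share R² of the variance left after baseline, the true level of a nominal 5% test is about 2 × [1 − Φ(1.96/√(1 − R²))]. This gives 4.4% at R² = 0.05, 3.9% at 0.10 and 2.8% at 0.20. These R² values are assumptions, and Table 3 does not report sex.

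**4. The activity difference (Table 3, completers).** Arm sizes are 25, 24, 26 and 25; means 157.2, 157.2, 116.8 and 155.5; SDs 66.2, 65.8, 68.6 and 65.9.

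- Within-arm mean square = 426,637/96 = 4,444, so the pooled SD is 66.7.
- Between-arm mean square = 30,564/3 = 10,188. F(3,96) = 10,188/4,444 = 2.29, p = 0.083. The article's statement is consistent with this.
- Tryptophan minus the mean of the other three arms = 116.8 − 156.6 = −39.8 points, or −0.60 SD. Tryptophan minus control = −40.4 points, or −0.61 SD.

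**5. How far adjusting for activity could move the tryptophan–control FGF-21 contrast.** Shift ≈ partial correlation of PASE with outcome × 0.606 × 70 pg/mL. The partial correlation is not in the article.

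| Assumed partial correlation | Shift (pg/mL) | Share of 44.82 |
|---|---|---|
| 0 | 0 | 0% |
| 0.1 | 4.2 | 9% |
| 0.2 | 8.5 | 19% |
| 0.3 | 12.7 | 28% |

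This separates model 2 from the other two analyses. The ANOVA and model 1 both omit activity.

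**6. The cost if any of the three could be reported.** Data were simulated with no treatment effect and the actual completer numbers per arm (4,000 runs per setting). The chance that at least one of the three tests is significant was about 7% to 10%, for assumed baseline correlations of 0.3 to 0.7 and PASE–outcome correlations of 0 to 0.2. With one model fixed in advance, the level is the nominal 5%.

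**The case against.** The best defence is that the section reads as an ordered sequence. Only model 1 is tied explicitly to assessing the intervention effect, model 2 builds on it, and all three are promised, so nothing says a result will be picked afterwards. Naming the primary model is also often left to an analysis plan, and one may exist unseen. This stands in part: selective reporting is something a reader might infer, not something the article states, and the 7% to 10% figure is conditional on it. The defence does not explain why the abstract names a model class that the methods do not use for these outcomes, or why a follow-up-only ANOVA is among the tests of effect.

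Four stronger readings are tempting and are not supported:

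- *The activity gap will change the tryptophan result.* This needs an association between activity and outcome given baseline, which the article does not supply. With no association, the shift is zero.
- *Ignoring baseline makes the test invalid or its standard errors wrong.* It costs power, but the test keeps its level. Only omitting the stratum makes the test conservative.
- *The baseline statement is false or hides the gap.* It is literally true of the 4-group test, and Table 3 prints the means. Testing the tryptophan arm against the rest gives p = 0.010, but that contrast was chosen after seeing the table and covers the 100 completers, not the 109 randomised. The size of the gap is informative; that p-value is not.
- *All primary outcomes are affected.* Self-reported appetite has its own method, and the stated questionnaire days are 4, 11, 18 and 25, with no pre-intervention score. Models 1 and 2 could not be fitted to it as written.

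**Conclusion.** The point holds for FGF-21, ghrelin and energy intake. The article states three between-arm analyses with none deciding, and its abstract names another. The clearest avoidable loss is the ANOVA without baseline: pairwise power about 0.61, against 0.73 to 0.88 for assumed correlations of 0.5 to 0.7. That loss is real only to the extent that the ANOVA is used to judge the effect. Leaving sex out of model 1 is a smaller defect that works against false positives, and its size depends on how much sex predicts outcome after baseline. The 0.6 SD activity difference means model 2 could disagree with the other analyses for the tryptophan arm; the documents do not allow the size to be stated. The change should be made before the analysis, but nothing here shows a biased comparison.

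**What to change.** - Drop the 1-way ANOVA of follow-up values as a test of effect, or label it descriptive.
- Before analysis, name one primary model for each outcome measured before and after the intervention. It should contain at least the baseline value and sex. Label the others sensitivity analyses.
- Where activity is a covariate, define it as the pre-intervention PASE score, not a measure taken during or after the intervention.
- Make the abstract and the Statistical Analysis section name the same model.
- Keep self-reported appetite under its generalized additive mixed model, with sex added.
- Describe the size of the activity difference in the text instead of relying on the baseline significance statement, and note that Table 3 covers completers.

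The data are already collected. The cost is wording and a few degrees of freedom out of about 96.
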